### Adverse events

All adverse events occurring during the study will be recorded and monitored. Data will be collected on falls, injuries, musculoskeletal problems, hypoglycemic episodes, major cardiovascular disease events, and any other events potentially related to the study procedures or interventions. All adverse events will be carefully evaluated and followed until symptoms or signs resolve or stabilize. Detailed records of management measures and outcomes will be maintained. Follow-up methods will be selected according to event severity and may include inpatient observation, outpatient follow-up, home visits, telephone follow-up, or written communication.

### Measures

#### Primary outcome measures.

The primary outcome measure of this study is skeletal muscle mass (SMM, kg) assessed using bioelectrical impedance analysis (BIA). Before measurement, participants will be instructed to avoid strenuous exercise, alcohol consumption, and excessive fluid intake, and to empty their bladders. Measurements will be performed under resting conditions according to a standardized protocol. Participants will stand barefoot on the electrode plates of the body composition analyzer, hold the hand electrodes with both hands, maintain an upright posture, and keep the upper limbs naturally abducted without touching the trunk. All measurements will be conducted by trained researchers during the same time period and under consistent environmental conditions to minimize the influence of diet, exercise, and hydration status. SMM will be recorded in kilograms (kg) to one decimal place.

#### Secondary outcome measures.

1) Grip Strength

Grip strength will be measured using a dynamometer (Jamar Plus+, USA) and recorded in kilograms. Participants will adjust the grip width to a comfortable position and perform maximal voluntary contraction for 3 seconds. Three measurements will be obtained for each hand and the highest value will be recorded. If the variation between measurements exceeds 10%, participants will rest for 10–15 minutes before repeat testing.

2) Skeletal Muscle Mass Index

Skeletal muscle mass index (SMI, kg/m²) will be assessed as a secondary outcome. Appendicular skeletal muscle mass (ASM, kg) will be measured using BIA with the same analyzer used for SMM assessment. Measurement procedures and precautions will be identical to those described for the primary outcome. SMI will be calculated as ASM divided by height squared: SMI = ASM (kg)/ height² (m²). Results will be expressed in kg/m² and recorded to two decimal places.

3) Body Fat Percentage

Body fat percentage will be measured using the same body composition analyzer under standardized conditions as described above. Results will be expressed as percentages (%) and recorded to one decimal place.

4) Physical Function Assessment

Physical function will be assessed using the Short Physical Performance Battery (SPPB), which includes a balance test, a 4-meter usual gait speed test, and a five-times sit-to-stand test. These components assess balance, walking ability, lower-limb muscle strength, and endurance, respectively. The balance test includes side-by-side, semi-tandem, and tandem standing positions. Each component will be scored from 0 to 4, yielding a total score ranging from 0 to 12, with higher scores indicating better physical function.

5) Quality of Life

Quality of life will be assessed using the MOS 36-item Short Form Health Survey (SF-36) [22]. The SF-36 evaluates eight domains of health-related quality of life: Physical Functioning (PF), Role-Physical (RP), Bodily Pain (BP), General Health (GH), Vitality (VT), Social Functioning (SF), Role-Emotional (RE), and Mental Health (MH). Scores for each domain will be converted to a 0–100 scale using the following formula: Converted Score = (Actual Score − Minimum Score for that Dimension)/ (Maximum Score for that Dimension − Minimum Score for that Dimension) × 100. The mean score for the eight domains will be calculated as the composite score, with higher scores indicating better quality of life.

### Statistical analysis

The primary efficacy analysis will be conducted according to the ITT principle, with all randomized participants analyzed in the groups to which they were originally assigned. Continuous variables will be summarized as means ± standard deviations or medians with interquartile ranges, as appropriate based on distribution, and categorical variables will be presented as frequencies and percentages. Baseline characteristics will be summarized by treatment group. Between-group comparisons at baseline will be performed using independent-samples *t* tests or Mann-Whitney U tests for continuous variables, and χ² tests or Fisher’s exact tests for categorical variables.

The primary analysis population will be the ITT population. A per-protocol set analysis will be conducted as a sensitivity analysis and will include participants who complete the intervention and follow-up assessments, meet prespecified adherence criteria, and have no major protocol deviations. Poor adherence will be defined as an intervention adherence rate of <50% per week for two consecutive weeks or an overall intervention adherence rate of <50% during the study period. The safety analysis population will include participants who receive at least one intervention session or complete at least one post-randomization safety assessment.

The sole primary confirmatory outcome will be SMM. The primary intervention effect will be defined as the adjusted between-group difference in change in SMM from baseline to the end of the 24-week intervention. The primary outcome will be analyzed using a linear mixed-effects model, with post-randomization SMM measurements as the dependent variable. Fixed effects will include group, time, the group-by-time interaction, and prespecified covariates, including age, sex, body weight, and baseline SMM. A participant-level random intercept will account for within-participant correlation arising from repeated measurements. Time will be modeled as a categorical variable to avoid imposing a linear change trajectory. The primary effect will be estimated from the group-by-time interaction at week 24, and the adjusted between-group mean difference, 95% confidence interval, and two-sided P value will be reported.

Secondary outcomes will include handgrip strength, skeletal muscle index, body fat percentage, SPPB score, and SF-36 quality-of-life score. Each secondary outcome will be analyzed using a linear mixed-effects model analogous to that used for the primary outcome. Fixed effects will include group, time, the group-by-time interaction, and prespecified covariates, including age, sex, body weight, and the baseline value of the corresponding outcome. Adjusted between-group differences, 95% confidence intervals, and two-sided P values will be reported. SMM will be the only primary confirmatory outcome, whereas secondary outcomes will provide supportive evidence regarding intervention effects. For analyses involving multiple secondary outcomes and repeated time points, the Benjamini–-Hochberg procedure will be applied to control the false discovery rate.

All available repeated-measures data will be included in the linear mixed-effects models using maximum likelihood estimation under the missing-at-random assumption. The extent, timing, and pattern of missing data, together with reasons for withdrawal or intervention discontinuation, will be summarized by group. For the primary outcome, a sensitivity analysis will be conducted using multiple imputation by chained equations. The imputation model will include randomized group, age, sex, height, body weight, BMI, baseline SMM, available follow-up SMM measurements, and other variables potentially associated with missingness or the primary outcome. Twenty imputed datasets will be generated and analyzed using the primary analysis model, with estimates pooled according to Rubin’s rules. If missingness in the primary outcome is substantial or the missing-data mechanism remains uncertain, a tipping-point analysis based on delta-adjusted multiple imputation will be performed. In this analysis, a series of prespecified unfavorable shifts will be applied to the imputed SMM values to assess the robustness of the primary conclusions under plausible missing-not-at-random assumptions.

Prespecified exploratory subgroup analyses will be performed by age and sex through inclusion of group-by-time-by-subgroup interaction terms in the linear mixed-effects model. Model assumptions will be evaluated using residual plots, normal Q-Q plots, and outlier diagnostics. If substantial heteroscedasticity or deviation from residual non-normality is detected, robust standard errors will be used in sensitivity analyses while retaining the primary model structure. Safety analyses will be primarily descriptive. Adverse events and serious adverse events will be summarized by group, severity, possible relationship to the intervention, and outcome. All statistical tests will be two-sided, and *P* < 0.05 for the primary outcome will be considered statistically significant. Statistical analyses will be performed using R software, version 4.4.2 (R Foundation for Statistical Computing, Vienna, Austria).

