### Sample size

The sample size was calculated using G-power 3.1 software. The calculation was based on a two-sided comparison of the mean change in skeletal muscle mass (SMM) between the two groups, with SMM prespecified as the sole primary confirmatory outcome. The expected effect size was derived from a previous Internet-based nutrition and exercise intervention study in older adults with sarcopenia [21]. In that study, the mean change in SMM was −0.10 kg in the control group and 1.09 kg in the comprehensive intervention group, corresponding to a between-group difference of 1.19 kg. Because the standard deviation of the SMM change score was not directly reported, it was conservatively estimated from the reported baseline and post-intervention standard deviations, assuming a pre-post correlation coefficient of 0.50. This yielded an estimated pooled standard deviation of approximately 2.70 kg and a Cohen’s d of approximately 0.44. Although the proposed intervention incorporates a knowledge graph-based recommendation system that may enhance intervention individualization, this moderate effect size was adopted to avoid overestimating the intervention effect. With a two-sided α level of 0.05, power of 0.80, and a 1:1 allocation ratio, 83 participants were required per group. Factoring an anticipated dropout rate of 20%, 104 participants will be enrolled in each group, resulting in a total sample size of 208 participants.

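### The primary model fits one baseline-SMM slope to all visits; if the true slope changes over time and dropout depends on baseline SMM differently by arm, the week-24 estimate can be biased even under missing at random

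*Protocol article*

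**What the plan says.** The Statistical analysis section of the Protocol article takes SMM after randomization as the dependent variable, with categorical time and a participant random intercept. The mean model is: "Fixed effects will include group, time, the group-by-time interaction, and prespecified covariates, including age, sex, body weight, and baseline SMM". Group-by-time is the only interaction in that list. Study design gives the visits after baseline as weeks 8, 16, 24 and 48, and the confirmatory effect is the group contrast at week 24.

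The secondary models have the same form, with age, sex, body weight "and the baseline value of the corresponding outcome". Missing data are handled "using maximum likelihood estimation under the missing-at-random assumption". A sensitivity analysis uses chained-equations imputation, with group, baseline SMM and the available follow-up SMM values among the predictors, and refits the primary model to 20 completed datasets. The only figure for the relation between baseline and later SMM is in Sample size: "assuming a pre-post correlation coefficient of 0.50".

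**The concern.** The plan makes time categorical so that no straight-line trajectory is imposed, yet it holds the relation between baseline and later SMM constant over 40 weeks (week 8 to week 48). A baseline value often predicts an early visit better than a late one. If so here, the common slope is a compromise that is wrong at week 24.

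With complete data and randomization this costs only some precision. With dropout, the participants still seen at week 24 may differ in baseline SMM between arms, and a wrong slope then adjusts wrongly for that difference. Dropout that depends only on arm and baseline SMM is missing at random, so the plan means to cover it. The estimate affected is the sole confirmatory one.

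**Working it through.** **The plan's own figure.** Two inputs come from Sample size. The source study's means are given as "corresponding to a between-group difference of 1.19 kg". The spread and standardised effect are stated separately: "This yielded an estimated pooled standard deviation of approximately 2.70 kg and a Cohen’s d of approximately 0.44".

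- d = 1.19 / 2.70 = 0.441, stated as 0.44.
- The stated requirement before dropout is: "With a two-sided α level of 0.05, power of 0.80, and a 1:1 allocation ratio, 83 participants were required per group". A two-sample t test (noncentral t) with d = 0.44 gives 83 per group, power 0.8045.
- The stated total rests on 20% dropout and 104 per group. 83 / (1 − 0.20) = 103.75, rounded up to 104; 2 × 104 = 208. The stated sizes are reproduced.

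**What the 0.50 implies.** SD of change = SD × √(2 − 2 × 0.50) = SD if the pre and post SDs are equal. Baseline SD is then about 2.70 kg and the end-of-intervention slope about 0.50. No other visit has a stated correlation.

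**Mechanism.** Let b24 be the true slope at week 24, b the common slope, and Δ the baseline difference (intervention minus control) among those observed at week 24. The leading error is (b24 − b) × Δ. Take slopes 0.7/0.6/0.5/0.4, with mean 0.55, and arms losing opposite ends (Δ = −1.02 kg in simulation): (0.50 − 0.55) × (−1.02) = +0.05 kg. The simulated bias is larger, because the model also predicts dropouts' missing values from their earlier residuals, which carry the same misfit.

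**Simulation.** Assumptions not in the documents: the slope patterns below; 20% monotone dropout by week 24; odds of dropout multiplied by 2.7 per SD of baseline (also 2 in the opposite-direction case). Age, sex and body weight were left out. Bias comes from 200,000 participants (simulation error about 0.01 kg), supplemented by 1,500 trials of 208. Week-24 bias of the planned common-slope model, in kg:

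| Slopes at weeks 8/16/24/48 | Same or no dependence | One arm only | Opposite directions |
|---|---|---|---|
| 0.5 throughout | about 0 | about 0 | about 0 |
| 0.97/0.95/0.92/0.88 | about 0 | about 0.02 | 0.01–0.03 |
| 0.6/0.55/0.5/0.45 | about 0 | 0.02–0.03 | 0.06 |
| 0.7/0.6/0.5/0.4 | about 0 | 0.05–0.06 | 0.07–0.14 |
| 0.9/0.7/0.5/0.3 | about 0 | 0.11–0.13 | 0.17–0.23 |

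With baseline-by-time added, bias was within about 0.02 kg of zero throughout. As shares of the planned effect: 0.06/1.19 = 5%, 0.14/1.19 = 12%, 0.23/1.19 = 19%.

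**Direction.** A separate run used 300,000 participants, log-odds 0.8 per SD, slopes 0.8/0.63/0.5/0.35 and true effect 1.19 kg. The common-slope model gave 1.13 when the intervention arm lost low baselines, 1.27 when it lost high ones, and 1.06 when the arms lost opposite ends. With the term it gave 1.20 each time. The one-arm shift is 0.07 kg (0.07/1.19 = 6%).

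**Cost of the term.** With truly constant slopes and 208 participants, the mean standard error goes from 0.3472 to 0.3472 (no dependence), 0.3474 to 0.3480 (one arm) and 0.3489 to 0.3516 (opposite): 0.3516/0.3489 = 1.008.

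**What the term leaves.** Under the null with opposite-direction dropout, rejection rates without and with it were 0.085 and 0.074 (slopes 0.7 to 0.4), and 0.149 and 0.102 (0.9 to 0.3). In the last pattern with no dropout dependence, the model with the term still rejected at 0.085: its mean standard error was 0.2999 against an empirical SD of 0.3452. That remainder comes from the covariance side of the model.

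**Multiple imputation.** Imputing each visit from its own regression on group, baseline and earlier visits, then fitting the unmodified common-slope model, gave week-24 bias of about 0.01 kg or less.

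**The case against.** A baseline main effect in a repeated-measures model is a common, prespecified choice, and with complete data it is unbiased under randomization. The documents say neither that the baseline slope changes nor that dropout will depend on baseline SMM differently by arm. The 0.50 is a cautious planning value applied to another study's data because its change SD was not reported; it says nothing about how the slope moves in this trial. If SMM tracks strongly throughout, the bias is 0.01–0.03 kg. Participants who stop the intervention are also encouraged to attend later assessments. All of this stands, and it limits the weight of the point.

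Three stronger readings are tempting. A reader might infer that arm-differential dropout on baseline SMM is enough to bias the estimate; it is not, because a flat slope gives no bias. A reader might infer that the imputation analysis inherits the fault because it ends in the primary model. Completed data under randomization are not biased by a common slope, and visit-by-visit imputation gives each visit its own slope, so the documents do not support that either. A reader might call the term free; it costs three parameters and a small amount of precision.

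The objection does not protect the primary estimate itself. A sensitivity analysis can expose the shift but does not remove it, and the planned fallback to robust standard errors leaves the mean model unchanged. If the two analyses disagreed, readers could blame the missing-data mechanism although missing at random held.

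**Conclusion.** The point holds in conditional form. As listed, the model imposes one baseline slope on four visits. Bias at week 24 needs both a changing true slope and dropout that depends on baseline SMM differently by arm; it can then go either way. It ranges from nil, through about 0.01–0.06 kg under mild change or high stable correlations, to about 0.07–0.23 kg under a steep decline, the top of that range only when the arms lose opposite ends. Against a standard error of about 0.35 kg, even the largest value is less than one standard error. Apart from the planning values for effect, SD, 0.50 correlation and 20% dropout, the inputs are assumptions, and omitting age, sex and body weight adds uncertainty. This is a worthwhile, inexpensive refinement and not a defect that invalidates the design.

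**What to change.** In Statistical analysis, add baseline-SMM-by-time to the primary fixed effects: group, time, group-by-time, baseline SMM, baseline-SMM-by-time, age, sex and body weight. Add the matching baseline-outcome-by-time term to each secondary model. Fit the same model to the imputed datasets, and state that each visit's SMM is imputed as its own variable.

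The cost is three extra parameters per model (four visits minus one), at most about 0.8% larger standard error in the cases checked, and no new data. Recruitment is still under way, so the change can be dated and documented before database lock. It does not repair the random-intercept covariance, which is a separate matter; conversely, a richer covariance alone would leave the single baseline slope in place.

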## Methods

### Study design

This single-blind, two-arm randomized controlled trial is designed to evaluate the effects of a knowledge graph-based lifestyle recommendation system on skeletal muscle mass, grip strength, skeletal muscle mass index, body fat percentage, physical function, and quality of life in patients with SO. Participants will be randomly assigned in a 1:1 ratio to either the intervention group or the control group. The intervention group will receive a 24-week lifestyle intervention aimed at increasing muscle mass and reducing weight, while the control group will receive conventional treatment and health education without personalized recommendations from the system. The total study duration is 48 weeks, comprising a 24-week intervention period followed by a 24-week follow-up period. Assessments will be conducted at baseline and at weeks 8, 16, 24, and 48, with week 24 marking the end of the intervention. Thereafter, both groups will enter a follow-up phase without systematic intervention and will be observed until week 48. The randomization sequence will be generated by a statistician using a computer-generated block randomization with block sizes of 4 or 6. Allocation concealment will be ensured through a password-protected centralized network system accessible only to independent registrars not involved in outcome assessment after completion of baseline assessments. Because of the nature of the lifestyle intervention, blinding of participants and intervention implementers is not possible. However, outcome assessors and statistical analysts will remain blinded throughout the study. All outcome assessments will be completed by uniformly trained independent assessors unaware of group allocation. Data managers and statistical analysts will remain blinded until database lock. Participants will be instructed not to disclose their group allocation to assessors, and an emergency unblinding procedure will be established if required. Intervention reporting will follow the Template for Intervention Description and Replication (TIDieR) checklist. The study protocol is developed in accordance with the SPIRIT statement (S1 File). Fig 1 and Fig 2 illustrate the proposed study timeline and procedures.

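### The random-intercept model ties all visits to one variance and one correlation, and robust standard errors never reach the confirmatory result; if SMM spread changes over time, week-8 and week-48 tests are miscalibrated and the week-24 test may be.

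*Protocol article*

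**What the plan says.** All references are to the Statistical analysis section of the protocol article unless stated otherwise.

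- **Model.** The primary outcome is analysed by a linear mixed-effects model "with post-randomization SMM measurements as the dependent variable". Fixed effects are group, time, their interaction, age, sex, body weight and baseline SMM. For the mean, "Time will be modeled as a categorical variable to avoid imposing a linear change trajectory". For the covariance, the only statement is "A participant-level random intercept will account for within-participant correlation arising from repeated measurements". No random slope, visit-specific variance or residual correlation is named.
- **Primary contrast.** "The primary effect will be estimated from the group-by-time interaction at week 24", tested two-sided at 0.05.
- **Visits (Study design).** "Assessments will be conducted at baseline and at weeks 8, 16, 24, and 48, with week 24 marking the end of the intervention".
- **Data used.** "All available repeated-measures data will be included in the linear mixed-effects models using maximum likelihood estimation under the missing-at-random assumption". Week 48 is not named here, but this wording takes it in.
- **Secondary outcomes.** They use an analogous model, and the Benjamini–Hochberg procedure is applied across outcomes and time points.
- **Diagnostics.** If substantial heteroscedasticity or non-normality is found, "robust standard errors will be used in sensitivity analyses while retaining the primary model structure".

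**The concern.** A random intercept with constant, independent residuals is compound symmetry. Every visit has the same variance, and two visits 8 weeks apart correlate exactly as strongly as two visits 40 weeks apart. Here the visits are unequally spaced, and the last falls 24 weeks after the intervention stops. The plan frees the mean from any assumed trajectory but leaves the covariance fully constrained.

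If the spread of SMM given baseline differs between visits, the model replaces each visit's own variance with an average over visits. Standard errors are then too large where spread is small and too small where it is large. The planned remedy does not change the confirmatory result: it is conditional, has no stated threshold, and is confined to sensitivity analyses. The multiple-imputation sensitivity analysis does not change it either, because the imputed data are analysed with the primary model.

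At stake are the error rate and interval coverage of the week-24 test, and of the week-8, 16 and 48 comparisons. For the secondary outcomes, the visit-wise P values feed a Benjamini–Hochberg procedure that presumes they are valid.

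**Working it through.** **1. The plan's own figure.** The Sample size section gives d = 0.44, two-sided α = 0.05, power 0.80 and 83 per group. A noncentral-t calculation with d = 0.44 and 83 per group gives power 0.8045. Then 83/0.80 = 103.75, so 104 per group and 208 in total. The figures reproduce. They rest on a t test at one time point and are not affected by this point.

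**2. What the model's standard error estimates.** Take complete data, categorical time and a group-by-time interaction, and read the primary effect as the adjusted group difference at week 24. The random-intercept model then assigns every visit the mean of the visit variances. At visit t:

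- SE ratio r(t) = SE(model)/SE(true) = √(mean of visit variances / variance at t)
- actual two-sided error of a nominal 5% test = 2 × [1 − Φ(1.96 × r(t))]

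Only relative variances matter, so the absolute scale drops out.

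**3. Inputs.** The article gives one change-score SD, 2.70 kg, with an assumed pre-post correlation of 0.50. With equal SDs before and after, the SD given baseline is 2.70 × √(1 − 0.50²) = 2.34 kg. No SD by visit is given, so the patterns below are assumptions that span a range.

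**4. Results, four visits, complete data.** Actual error at nominal 5%:

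| Assumed pattern over weeks 8, 16, 24, 48 | Week 8 | Week 16 | Week 24 | Week 48 |
|---|---|---|---|---|
| Constant variance | 5.0% | 5.0% | 5.0% | 5.0% |
| SD changes by 1% of its week-24 value per week (0.84, 0.92, 1, 1.24) | 1.8% | 3.1% | 4.8% | 11.0% |
| SD 1.5, 2.0, 2.34, 2.9 kg | 0.3% | 2.8% | 6.0% | 12.9% |
| Variance proportional to time (8, 16, 24, 48) | 0.1% | 1.6% | 5.0% | 16.6% |
| Variance grows to week 24, then flat (8, 16, 24, 24) | 0.3% | 3.8% | 9.0% | 9.0% |
| SD proportional to time | <0.1% | <0.1% | 2.1% | 24.8% |

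Three worked entries:

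- Variance proportional to time: the mean of 8, 16, 24 and 48 is 24, so r(24) = √(24/24) = 1.00 and the week-24 test is exact. At week 48, r = √(24/48) = 0.707.
- Growth then plateau: the mean of 8, 16, 24 and 24 is 18, so r(24) = √(18/24) = 0.866, error 9.0%.
- SD proportional to time: the mean of 64, 256, 576 and 2304 is 800, so r(24) = √(800/576) = 1.18, error 2.1%. The test is conservative.

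**5. Simulation check.** 1,500 null trials per scenario, 104 per arm, decaying correlation, with and without 20% dropout. The Monte Carlo standard error at 5% is √(0.05 × 0.95/1500) = 0.6 points. Rejection rates, random intercept versus unstructured covariance:

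| Scenario and visit | Complete data | 20% dropout |
|---|---|---|
| SD 1.5 to 2.9 kg, week 24 | 6.3% vs 5.2% | 6.7% vs 5.2% |
| SD 1.5 to 2.9 kg, week 48 | 12.9% vs 5.7% | 15.0% vs 4.1% |
| Growth then plateau, week 24 | 9.6% vs 5.5% | 11.1% vs 5.4% |
| Variance proportional to time, week 24 | 5.7% vs 5.5% | 6.2% vs 5.5% |
| Variance proportional to time, week 48 | 17.7% vs 5.0% | not reported |

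In a separate run of the same size, cluster-robust standard errors on the planned model gave about 4% to 6% at every visit in every growing-variance scenario.

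**6. ML rather than REML.** The plan fits "using maximum likelihood estimation under the missing-at-random assumption". With 166 participants and about six between-participant parameters, the SE shrinks by roughly √(160/166) = 0.98. Then 2 × [1 − Φ(1.96 × 0.98)] is about 5.4%, a slight effect.

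**The case against.** **A reader might infer that the confirmatory P value is wrong.** The documents do not support that. With all four visits in the model, the week-24 error is near nominal under several forms of growth, inflated under a plateau, and conservative if the SD is proportional to time. Not even the direction is known. Growth of spread is itself an assumption, and with constant variance the week-24 test holds its level. This objection stands and limits the finding.

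**A reader might quote larger week-24 errors from a model of weeks 8, 16 and 24 only.** For example, SDs of 1.5, 2.0 and 2.34 kg give a mean variance of (2.25 + 4.00 + 5.48)/3 = 3.91, r = √(3.91/5.48) = 0.845 and an error of 9.8%. The wording on all available repeated measures does not suggest that model, so such figures should not be attributed to this plan.

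**The plan already foresees the problem.** Diagnostics and robust standard errors are specified, and the latter would expose the misfit. In addition, the planned imputation step is not stated to impose compound symmetry. This stands in part: a detected misfit would be reported, but the primary P value and interval would not change.

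**Covariance detail belongs in the analysis plan.** Degrees of freedom and convergence rules do, and their absence is no fault. But the article does make a choice. It names the random intercept as what accounts for within-participant correlation, and it retains that structure after failed diagnostics. An unseen analysis plan could add visit-specific residual variances, which would remove much of the concern.

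**The inflation falls mainly on non-confirmatory tests.** This is correct for week 48. Those tests still carry the message about durability after the intervention ends.

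**Conclusion.** The point holds as a robustness weakness that should be corrected, not as a demonstrated error in the primary result. As written, the primary and secondary models impose equal variances and equal correlations across unequally spaced visits, and the confirmatory P value and interval keep that constraint even if diagnostics contradict it.

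The size depends on visit-specific SDs that the article does not give. Under the growth patterns examined, the clearest exposure is at the ends of the schedule: tests that are too conservative at week 8 and too liberal at week 48. For the primary week-24 contrast, the complete-data range is about 2% to 9%. Dropout raised the simulated week-24 error by 0.4 to 1.5 points, to 11.1% in the least favourable scenario. These figures assume constant independent residuals around the random intercept, all four visits in the model, and the primary effect read as the group difference at week 24. The use of ML adds little.

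**What to change.** Keep the fixed effects. Replace the random intercept with an unstructured within-participant covariance across the four post-randomization visits, fitted by REML with Kenward-Roger or Satterthwaite degrees of freedom, for the primary and all secondary outcomes. Prespecify a fallback for non-convergence, for example heterogeneous Toeplitz, then random intercept with cluster-robust standard errors. State that week 48 is in the model.

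If the random intercept is kept, the minimum change is to make cluster-robust standard errors part of the primary analysis for every outcome, without a diagnostic trigger.

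The cost is a change of wording, ten covariance parameters (4 variances + 6 covariances) instead of two, and a fallback rule. With 208 participants and four visits this is easily supported. The sample size of 83 per group, 104 after dropout and 208 in total is unchanged. Recruitment is still open according to the Trial status section, so the change can be prespecified before analysis.
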